# Effect of perioperative sigh ventilation on postoperative hypoxemia and pulmonary complications after on-pump cardiac surgery (E-SIGHT): study protocol for a randomized controlled trial

**DOI:** 10.1186/s13063-024-08416-y

**Published:** 2024-09-04

**Keywords:** Postoperative hypoxemia, Postoperative pulmonary complications, Cardiac surgery, Cardiopulmonary bypass, Sigh, Mechanical ventilation

## Abstract

**Background:**

Postoperative hypoxemia and pulmonary complications remain a frequent event after on-pump cardiac surgery and mostly characterized by pulmonary atelectasis. Surfactant dysfunction or hyposecretion happens prior to atelectasis formation, and sigh represents the strongest stimulus for surfactant secretion. The role of sigh breaths added to conventional lung protective ventilation in reducing postoperative hypoxemia and pulmonary complications among cardiac surgery is unknown.

**Methods:**

The perioperative sigh ventilation in cardiac surgery (E-SIGHT) trial is a single-center, two-arm, randomized controlled trial. In total, 192 patients scheduled for elective cardiac surgery with cardiopulmonary bypass (CPB) and aortic cross-clamp will be randomized into one of the two treatment arms. In the experimental group, besides conventional lung protective ventilation, sigh volumes producing plateau pressures of 35 cmH_2_O (or 40 cmH_2_O for patients with body mass index > 35 kg/m^2^) delivered once every 6 min from intubation to extubation. In the control group, conventional lung protective ventilation without preplanned recruitment maneuvers is used. Lung protective ventilation (LPV) consists of low tidal volumes (6–8 mL/kg of predicted body weight) and positive end-expiratory pressure (PEEP) setting according to low PEEP/FiO_2_ table for acute respiratory distress syndrome (ARDS). The primary endpoint is time-weighted average SpO_2_/FiO_2_ ratio during the initial post-extubation hour. Main secondary endpoint is the severity of postoperative pulmonary complications (PPCs) computed by postoperative day 7.

**Discussion:**

The E-SIGHT trial will be the first randomized controlled trial to evaluate the impact of perioperative sigh ventilation on the postoperative outcomes after on-pump cardiac surgery. The trial will introduce and assess a novel perioperative ventilation approach to mitigate the risk of postoperative hypoxemia and PPCs in patients undergoing cardiac surgery. Also provide the basis for a future larger trial aiming at verifying the impact of sigh ventilation on postoperative pulmonary complications.

**Trial registration:**

ClinicalTrials.gov NCT06248320. Registered on January 30, 2024. Last updated February 26, 2024.

**Supplementary Information:**

The online version contains supplementary material available at 10.1186/s13063-024-08416-y.

## Background

Postoperative pulmonary complications (PPCs) remain a frequent event after on-pump cardiac surgery and mostly characterized by pulmonary atelectasis [1]. Atelectrauma, denoting the cyclic expansion and collapse of atelectatic lung regions, and volutrauma, involving excessive distension of neighboring patent alveoli, are recognized as pivotal contributors to ventilator-induced lung injury (VILI) subsequent to atelectasis [2, 3]. This injurious sequence is associated with hypoxemia, pneumonia, ventilator-induced lung injury, and acute respiratory distress syndrome (ARDS), thereby engendering escalated healthcare resource utilization, delayed patient mobilization, prolonged reliance on supplementary oxygen or mechanical ventilation, and protracted hospitalization [4].

Patients undergoing on-pump cardiac surgery are subject to a convergence of pulmonary insults. The administration of general anesthesia combined with invasive mechanical ventilation initiates a distinctive lung insult recognized as ventilator-induced lung injury [5]. Additionally, cardiac surgery introduces a secondary insult: cardiopulmonary bypass (CPB) elicits a systemic inflammatory response [6], while the application of the aortic cross clamp contributes to pulmonary ischemic injury [7]. Moreover, the frequent necessity for blood transfusions and the experience of postoperative pain significantly contribute to the heightened incidence of postoperative pulmonary complications (PPCs) [8, 9]. Pulmonary atelectasis is very common in this context.

The implementation of targeted perioperative ventilatory strategies aimed at mitigating pulmonary atelectasis and postoperative pulmonary complications (PPCs) represents a well-established approach [10–12]. Numerous investigations have described the concept of lung protective ventilation. Inspired by the results obtained in critical care medicine in patients with acute respiratory distress syndrome (ARDS), the use of low tidal volumes (6–8 mL/kg predicted body weight) has spread to the operation room and there is now an established consensus [13]. However, the use of low tidal volumes may precipitate the constitution of pulmonary atelectasis in the poorly ventilated, dependent regions of the lung [14]. Constant low tidal volume ventilation [15] combined with multiple insults from cardiac surgery may engender significant perturbations in lung surfactant homeostasis.

Surfactant, pivotal for maintaining low surface tension and averting atelectasis, undergoes continuous inactivation and/or depletion, necessitating ongoing secretion for its preservation [15]. Meanwhile, animal studies revealed that the diminishment of large aggregate forms of lung surfactant precedes the abnormalities in lung permeability and gas exchange [16]. Mechanical strain on type II pneumocytes, induced notably by large tidal volumes (VTs), represents the strongest stimulus for surfactant release [17–19]. Pattle’s seminal observations nearly six decades ago underscored the significance of yawning or deep breaths in augmenting surfactant recruitment to the alveolar lining film [20]. He postulated that the prevention of deep breaths could precipitate the collapse of alveolar, proposing periodic maximal inflations during mechanical ventilation to forestall such occurrences.

Short-term administration of sighs improves compliance and gas exchange, reducing ventilation heterogeneity and regional lung strain, reversing and preventing atelectasis, and mitigating the production of inflammatory cytokines [21–23]. Recent studies also suggested that sighs seem to be safe when administered to patients with lung injury or trauma [24, 25]. This single-center, randomized study is going to be conducted in patients undergoing scheduled on-pump cardiac surgery to test whether incorporating sigh to perioperative protective ventilation was safe and the efficacy to reduce postoperative hypoxemia and pulmonary complications.

The primary objective is to assess the efficacy of the perioperative sigh breaths in terms of oxygenation during post-extubation period, assessed by time-weighted average SpO_2_/FiO_2_ ratio during the initial post-extubation hour. Key secondary objectives are to assess the severity of respiratory failure by post-extubation day 7 and PPCs by postoperative day 7.

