### Sample size and power

The study determined a sample size of 192 patients (96 per group) with a 5% dropout rate and a *P* value of 0.05 to achieve 90% power in detecting a 10% increase in time-weighted average SpO_2_/FiO_2_ during the initial post-extubation hour in the experiment strategy group, compared to the control group. The control group’s mean time-weighted average SpO_2_/FiO_2_ was estimated to be 294 with a standard deviation of 60, based on previous research [30], and the 10% difference between groups was determined from previous work showing that a decrease of 10% from baseline in PaO_2_/FiO_2_ was clinically meaningful in lung injury induced by ventilatory strategies [31–33]. A dropout rate of 5% was deemed acceptable for informed consent withdrawals post-enrollment.

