### Statistical analysis

The data will be analyzed using R (version 4.3.3). The primary analysis will be carried out according to the intention-to-treat principle. The full analysis population (including all subjects who will be randomized and will be at least evaluated at baseline) will be used in the primary analysis. No interim analysis is planned. In case of missing data, the reason and mechanism for missing data will be explored. For missing data greater than 20%, multiple imputation may be considered as a sensitivity analysis to evaluate the treatment effect and associated standard error as appropriate.

Categorical variables are reported as number and percentage. Normally distributed variables are reported as mean and SD, non-normally distributed as median and IQR. Normal distribution of data will be assessed with the Kolmogorov–Smirnov test or the Shapiro–Wilk test. To compare continuous variables between experimental strategy and control strategy groups, Student’s *t*-test or Mann–Whitney *U* test will be used, as appropriate. Categorical variables will be compared using the Fisher exact test or likelihood ratio tests. The baseline and intraoperative parameters will be described per group (“experimental strategy” and “control strategy”) in accordance with the Consolidated Standards of Reporting Trials (CONSORT) guidelines.

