The time-weighted average SpO_2_/FiO_2_ ratio will be compared as continuous variable. And treatment effects of primary outcome will also be analyzed according to the following subgroups: (1) age; (2) duration of cardiopulmonary bypass; (3) preoperative pathological chest image; (4) red cell transfusion during surgery. For secondary outcomes, the scores of pulmonary complications and severity of respiratory failure will be analyzed through Mann–Whitney *U* tests and multivariable ordinal logistic regression by estimating the common odds ratio for a shift in the direction of a better outcome on the modified scale. The proportion of other secondary endpoints (use of high-flow nasal cannula or non-invasive ventilation, use of new invasive mechanical ventilation, in-hospital mortality, adverse events) will be compared between the groups. Non-ventilatory support days and invasive mechanical ventilation days by postoperative day 7 will be compared between groups as continuous variables. Multiple comparison corrections will be performed for non-independent outcomes. The duration of ICU and hospital stay was compared using Kaplan–Meier curves and log-rank tests. The censoring was performed at postoperative day 28, and the time to event was the time from surgery end to ICU and hospital discharge. Patients who died before leaving the ICU or hospital were censored as nondischarged at day 28. A 2-sided *P* value < 0.05 was considered statistically significant.

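### The trial says it will test whether sighs are safe, but its only between-group criterion for harms is a difference test at P < 0.05, which for uncommon events at 96 per arm cannot show safety

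*Protocol article*

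**What the plan says.** The last part of the Background gives the study's purpose as "to test whether incorporating sigh to perioperative protective ventilation was safe and the efficacy to reduce postoperative hypoxemia and pulmonary complications". The objectives that follow concern efficacy only: "The primary objective is to assess the efficacy of the perioperative sigh breaths in terms of oxygenation during post-extubation period", with respiratory failure and pulmonary complications as key secondary objectives.

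The Study endpoints section lists three adverse events by postoperative day 7: use of high-dose vasopressors, radiologically defined barotrauma, and reoperation before the 12th postoperative hour. In-hospital mortality is a separate secondary endpoint.

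The Statistical analysis section puts these harms in a list of secondary proportions: "in-hospital mortality, adverse events) will be compared between the groups". The method is "Categorical variables will be compared using the Fisher exact test or likelihood ratio tests", and the threshold is "A 2-sided *P* value < 0.05 was considered statistically significant". No excess risk to be ruled out is stated, and no interval is attached to the harms.

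The Sample size section sets 192 patients (96 per group, 5% dropout) "to achieve 90% power in detecting a 10% increase in time-weighted average SpO_2_/FiO_2". No adverse event enters that calculation, and the article gives no expected rate for any of them.

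**The concern.** A difference test asks whether the data contradict equal risk. A question about safety asks how large an excess the data still allow. The article poses the second question and supplies only the first tool. With few events, a non-significant test is the likely outcome whether or not harm is present, so it does not separate the two cases.

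This matters here because the article says the results could provide a ready-to-use treatment and will be the basis for a larger trial. With no interim analysis and no data monitoring committee, the final comparison is the only between-group look at harm that the article describes.

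A second problem is that two tests are named for categorical variables with no rule for choosing between them. At low counts they can disagree sharply.

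**Working it through.** **Inputs from the article.** 96 per arm (about 91 after 5% dropout), 1:1 allocation, two-sided alpha 0.05, Fisher exact or likelihood ratio test; control mean 294, SD 60, and a 10% increase (29.4 units) for the primary endpoint.

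**Inputs assumed.** Control event rates of 1% to 10%, because the article gives none.

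**Step 1: the plan's own figure.** n per arm = 2(1.960 + 1.282)² × 60² / 29.4² = 2 × 10.51 × 3600 / 864.4 ≈ 87.5, so 88. The t-test version gives 88.5, so 89. Dividing by 0.95 gives 94 per arm, 188 in total, close to the stated 192. T-test power at 91 per arm is 90.8%. The size is sound for oxygenation and was set for nothing else.

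**Step 2: chance of missing a true excess.** Let X and Y be independent binomials (96, p0) and (96, p1) for control and sigh. Power is the sum of P(X = i)P(Y = j) over all tables with two-sided P < 0.05 and j > i. The likelihood ratio statistic is G = 2 Σ O ln(O/E), referred to 3.841. The miss rate is 1 − power.

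| Control → sigh | Fisher | Likelihood ratio |
|---|---|---|
| 1% → 3% | 97% | 76% |
| 2% → 6% | 84% | 65% |
| 5% → 15% | 44% | 33% |
| 10% → 30% | 7% | 5% |
| 2% → 4% | 96% | 83% |
| 5% → 10% | 82% | 73% |
| 10% → 20% | 58% | 50% |

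With 91 per arm the rates are slightly higher (2% → 6%: 86% / 66%).

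**Step 3: size needed.** For 80% power to detect a tripling (normal approximation, no continuity correction), n per arm is 769 from 1%, 376 from 2%, 245 from 3% and 141 from 5%. The trial has 96.

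**Step 4: what an interval would show.** The Newcombe interval combines the Wilson limits (l, u) of each arm. Its upper limit for sigh minus control is d + √[(u₁ − p₁)² + (p₀ − l₀)²], where 1 is sigh and 0 is control.
- 2 v 2 events: p = 0.0208, Wilson limits 0.0057 and 0.0728. Upper limit = √(0.0520² + 0.0151²) = 0.054. The interval is −5.4 to +5.4 percentage points.
- 2 (control) v 7 (sigh): d = 5/96 = 0.052, and the upper limit for 7/96 is 0.1429. Upper limit = 0.052 + √(0.0700² + 0.0151²) = 0.124. The interval is −1.2 to +12.4 points, although P = 0.17 (Fisher) and 0.08 (likelihood ratio).

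**Step 5: do the two tests agree?** With a true rate of 2% in both arms, the chance of P < 0.05 is 0.4% for Fisher and 9.4% for the likelihood ratio test, against a nominal 5%. For 0 v 5 events, Fisher gives P = 0.059 and the likelihood ratio test P = 0.008.

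**The case against.** Several points on the other side are fair, and they limit the finding.

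- **No safety inference from P > 0.05 is stated.** A reader might infer that the plan commits to calling sighs safe if the test is not significant. The article says only that proportions will be compared, so that would be a prediction about the report. What stands is that the article offers no other between-group method for answering the question it poses.
- **Safety is not a listed objective.** It appears in one sentence of the Background; the primary and key secondary objectives are efficacy, and the Discussion speaks of feasibility and preliminary efficacy. Sizing a trial on its primary endpoint is ordinary. This keeps the point away from the main conclusions but leaves the published aim as worded.
- **No single miss rate applies.** It is tempting to say a tripling of barotrauma would be missed 65% to 85% of the time. That holds only near an assumed 2% control rate. Barotrauma is broadly defined on imaging, with daily X-rays in the ICU and a planned chest CT, so the detected rate could be well above 2%. From 10%, a tripling would almost always be detected.
- **There are other safety provisions.** Sighs are suspended for low systolic pressure and interruptions are analysed. Adverse events are recorded, assessed for causality and reported. The difference test is the only between-group statistical criterion for these harms, not the only safety measure.
- **An unseen analysis plan may add intervals.** That is possible, and their absence from an article is not the finding. The finding is that the stated aim does not match the stated method and size.

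**Conclusion.** The point holds in a limited form. The article states a safety test, and the criterion it gives for harms cannot answer that test when events are uncommon. For control rates up to 5%, a true tripling would be missed at least a third of the time by either test. A doubling would be missed at least half the time at each control rate checked (2%, 5%, 10%). Even equal counts of 2 v 2 leave an excess of about 5 percentage points open.

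These figures rest on assumed control rates and on 96 evaluable patients per arm. If harms are common (control rate near 10%), a tripling would be detected, though a doubling still would not be reliably.

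Leaving the choice between the two named tests open adds a smaller defect: at a 2% event rate their true sizes are about 0.4% and 9%. The primary and key secondary efficacy conclusions are unaffected.

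**What to change.** **Statistical analysis section.** Take the adverse events and in-hospital mortality out of the list of proportions judged at P < 0.05. Report each as events/N per arm, with the risk difference (sigh minus control) and a two-sided 95% confidence interval by a small-count method such as Newcombe. State that P > 0.05 will not be taken as evidence of safety. If a test is kept for these outcomes, name Fisher exact only.

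**Background.** Reword the safety aim as estimating the excess risk of adverse events with sighs. Add that at 96 per arm even 2 v 2 events leaves an excess of about 5 percentage points open.

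**Cost.** A few sentences in the analysis text and one in the aim, with no new patients, data or procedures. The downside is that the report will show wide intervals and cannot offer an unqualified conclusion that sighs are safe.

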## Methods/design

### Trial design

This study is an investigator-initiated, prospective, single-center, randomized, controlled, parallel group, clinical trial with a 1:1 allocation. Participants, care providers, and outcomes assessor will be blinded to the group allocation. Two perioperative ventilatory strategies in cardiac surgery with cardiopulmonary bypass are compared: (1) experimental strategy: intermittent sigh breaths plus perioperative lung protective ventilation; (2) control strategy: conventional perioperative lung protective ventilation (Fig. 1). The study will be conducted in adherence to the principles of the World Medical Association’s Declaration of Helsinki and in accordance with the Medical Research Involving Human Subjects Act (WMO). Ethics approval was obtained before starting enrollment and consent will be obtained for each patient following local regulations. The Institutional Review Board of the Zhongda Hospital approved the protocol on 22 Feb 2024 under reference number 2024ZDSYLL037-P01. The trial was registered at www.clinicaltrials.gov with code NCT06248320 in Jan 2024. First patient was enrolled in 25 Feb 2024. The Standard Protocol Items: Recommendation for Interventional Trials (SPIRIT) checklist can be found in Additional file 1 and the SPIRIT figure is included in the main body of the manuscript (Fig. 2).

**Fig. 1 Fig1:**
[figure not shown]
Consolidated Standards of Reporting Trials (CONSORT) diagram for the E-SIGHT trial. ECMO, extracorporeal membrane oxygenation; IABP, intra-aortic balloon pump; CPAP, continuous positive airway pressure; LPV, lung protective ventilation

**Fig. 2 Fig2:**
[figure not shown]
E-SIGHT trial schedule during the study period. *HFNC* high-flow nasal cannula, *ICU* intensive care unit, *IMV* intensive mechanical ventilation, *NIV* non-invasive ventilation, *PaO*_*2*_ arterial pressure in oxygen, *POD* postoperative day, *SpO*_*2*_ pulse oximetry, *FiO*_*2*_ inspired oxygen fraction

### Study setting

This clinical trial will be conducted at Zhongda Hospital, a tertiary teaching hospital affiliated to Southeast University, situated in Nanjing, China. This high-volume university hospital performs a minimum of 400 cardiac surgical operations involving CPB annually.

### Eligible criteria

#### Inclusion criteria

Patients are eligible if they are 18 years or older, scheduled for elective cardiac surgery with general anesthesia, conventional CPB, and aortic cross clamp. Signed, informed consent provided by the patient or the legally authorized representatives will be obtained precede the study inclusion.

#### Exclusion criteria

Considering the minimal impact of sigh breaths on individuals with pre-existing hypoxemia resulting from chronic lung diseases, and those with high risk of developing lung dysfunction due to pre-existing severe cardiac impairment or other non-pulmonary risk factors not attributable to perioperative ventilation strategy, these individuals will be excluded from the study.

The exclusion criteria are:Emergent surgery including aortic dissection, cardiac rupture, and active endocarditis surgeryLeft ventricular assist device implantationPatients who are anticipated to require continuously perioperative circulatory support with extracorporeal membrane oxygenation (ECMO) or intra-aortic balloon pump (IABP)Chronic pulmonary disease requiring long-term home oxygen therapy or continuous positive airway pressure support (CPAP)Receiving invasive mechanical ventilation within 7 days prior to surgeryPreoperative shockObstructive sleep apnea syndrome (OSAS) requiring intermittent non-invasive ventilator supportPreoperative left ventricular ejection fraction (LVEF) < 40%Pulmonary arterial systolic pressure > 50 mmHgRedo surgery within the same hospitalization

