The secondary endpoints include:Respiratory failure by post-extubation day 7No respiratory failure: SpO_2_ ≥ 90% after breathing ambient air for 10 min (excluding hypoventilation)Mild respiratory failure: SpO2 < 90% or PaO2 < 60 mmHg after breathing ambient air for 10 min (excluding hypoventilation) and corrected with 1–3 L/min with a nasal cannulaModerate respiratory failure: SpO2 < 90% or PaO2 < 60 mmHg despite a 3 L/min oxygen supply with a nasal cannula (excluding hypoventilation) and corrected with an oxygen supply from 4 to 10 L/min with a face maskSevere respiratory failure: SpO2 < 90% or PaO2 < 60 mmHg despite a 10 L/min oxygen supply with a face mask (excluding hypoventilation) and corrected with an oxygen supply > 10 L/min with a high-flow face mask or with non-invasive ventilation or with high-flow nasal oxygen therapy or with invasive mechanical ventilationSeverity of postoperative pulmonary complications by postoperative day 7, scored on an ordinal scale ranging from 0 to 5, using a modified definition of pulmonary complications [10]Grade 0: No symptoms or signalsGrade 1: One of the following: dry cough, abnormal lung findings and temperature 37.5 °C or higher with normal chest radiograph, or dyspnea without other documented causeGrade 2: Two of the following: productive cough, bronchospasm, hypoxemia (SpO2 90%) at room air, atelectasis with gross radiological confirmation (concordance of 2 independent experts) plus either temperature higher than 37.5 °C, or abnormal lung findings, hypercarbia (PaCO2 > 50 mmHg) requiring treatmentGrade 3: One of the following: pleural effusion resulting in thoracentesis, pneumonia, pneumothorax, extended noninvasive ventilation or high-flow nasal cannula, or reintubation lasting less than 48 hGrade 4: Reintubation or invasive mechanical ventilation for 48 h or moreGrade 5: Death before hospital dischargeInvasive mechanical ventilation (IMV) days in ICU by postoperative day 7Duration of invasive mechanical ventilation by postoperative day 7, initiated from ICUadmission.Use of high-flow nasal cannula or non-invasive ventilation by postoperative day 7.Use of new invasive mechanical ventilation by postoperative day 7.No ventilatory support days by postoperative day 7.No ventilatory support days are defined as days without invasive mechanical ventilation,high-flow nasal cannula, and non-invasive ventilation.In-hospital mortalityDeath occurred during hospital stay, time frame from the day of surgery up to hospitaldischarge or death, maximum censoring at day 28 after surgery.ICU length of stayDays since surgery until ICU discharge. The censoring will be performed at day 28 aftersurgery. Patients dying before leaving the ICU were censored as not discharged from ICU atday 28 after surgery.Length of hospital stayDays since surgery until hospital discharge. The censoring was performed at 28 days. Patientsdying before leaving the hospital were censored as not discharged from hospital at day 28.Adverse events by postoperative day 7:Use of high-dose vasopressors (> 1 µg/kg/min of norepinephrine)Postoperative barotraumaDefined as the presence of radiological evidence suggesting pneumothorax, mediastinal emphysema, new-onset pulmonary emphysema, or subcutaneous emphysema.Reoperation before the 12th postoperative hour

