#### Baseline data

The following baseline data are collected after the patient’s inclusion: gender, age, height, weight, BMI, smoking status, history of COPD or asthma with chronic inhalation therapy, American Society of Anesthesiologists (ASA) score, Euroscore II, lower respiratory tract infection in the past 3 months, abnormal preoperative chest imaging, cardiovascular status (diabetes mellitus, arterial hypertension, dyslipidemia, liver disease, previous acute myocardial infarction, history of cardiac surgery, left ventricular ejection fraction, echocardiographic right ventricular distention defined by a right ventricle/left ventricle ratio > 1, brain natriuretic peptide level, cardiac troponin I level), and status of preoperative creatininemia > 3 mg/dL.

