#### Intraoperative variables

During the surgery, the anesthesiologist in charge of the patient will record the following variables: type of surgery (coronary artery bypass graft, valve surgery, aortic surgery, mixed surgery, none of the above), site of vascular graft harvesting (great saphenous vein, mammary artery, radial artery), number of vessels for coronary arterial bypass, CPB duration, aortic cross clamp duration, surgical duration, intraoperative fluid volume (crystalloid and colloid), fluid balance during surgery, use of blood transfusions (include red cell, platelets, or plasma), use of inotropic agents and vasopressors, use of rescue therapy. Gas exchange parameters (arterial blood partial pressure of carbon dioxide, arterial blood partial pressure of oxygen, PaO_2_/FiO_2_), mechanical ventilation parameters (tidal volume, respiratory rate, positive end-expiratory pressure, inspired oxygen fraction, minute ventilation), and respiratory mechanics (peak airway pressure, plateau pressure, driving pressure, respiratory system compliance) will be recorded within 10 min after endotracheal intubation and within 10 min after the conclusion of the surgery.

For patients allocated to the experimental strategy, further details of the experimental intervention will be documented as follows: the total duration of sigh breaths during the intraoperative period. Hemodynamic variables, including heart rate, systolic arterial pressure, diastolic arterial pressure, and mean arterial pressure, will be assessed during the first and second intraoperative sigh breath. Any interruptions in sigh breaths during the intraoperative period will also be documented.

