#### Postoperative variables

Gas exchange parameters, mechanical ventilation parameters, and respiratory mechanics will be recorded within 10 min, 2 h, and 4 h after ICU admission. Use of rescue therapy will also be recorded during invasive mechanical ventilation in postoperative days. For patients allocated to the experimental strategy, total duration of sigh breaths during the postoperative period, hemodynamic variables, and any interruption of sigh breaths will be documented.

For outcome assessments, SpO_2_/FiO_2_ will be assessed during the initial post-extubation hour, measured every 15 min. Then, patients are visited, twice a day, every postoperative day until postoperative day 7, in order to assess the presence of PPCs or other secondary endpoints. Hospital mortality, length of hospital stay, and length of ICU stay will be assessed upon hospital discharge, death, or postoperative day 28, whichever occurred first. The need for supplemental oxygen will be evaluated at each visit by measuring SpO_2_ and/or PaO_2_ after 10 min of breathing room air. Lung auscultation and daily symptoms of cough and expectoration will also be assessed at each visit. A daily chest X-ray will be prescribed during ICU stay. In the surgical ward, a chest X-ray will be prescribed at the discretion of the attending physician. A chest CT scan will be conducted between the third and fifth postoperative day.

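### The exclusion for chronic hypoxemia is narrower than its stated rationale, and the respiratory-failure scale has no preoperative reference, so long-standing hypoxemia can be graded as a postoperative event

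*Protocol article*

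**What the plan says.** **Eligibility.** The Exclusion criteria section of the protocol article first gives reasons. One is "Considering the minimal impact of sigh breaths on individuals with pre-existing hypoxemia resulting from chronic lung diseases", and the sentence ends "these individuals will be excluded from the study". The operative list follows. Its only item on chronic lung disease is "Chronic pulmonary disease requiring long-term home oxygen therapy or continuous positive airway pressure support (CPAP". Sleep apnea on intermittent non-invasive support and invasive ventilation within the 7 days before surgery are separate items. No criterion uses SpO2 or PaO2.

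**Baseline data.** The respiratory entries are smoking, "history of COPD or asthma with chronic inhalation therapy", recent lower respiratory infection and abnormal chest imaging. No room-air oxygenation value is listed. The first gas-exchange values, under Intraoperative variables, "will be recorded within 10 min after endotracheal intubation and within 10 min after the conclusion of the surgery".

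**Endpoints.** Under Study endpoints, mild respiratory failure begins at "SpO2 < 90% or PaO2 < 60 mmHg after breathing ambient air for 10 min", subject to exclusion of hypoventilation and correction with low-flow nasal oxygen. Room-air hypoxemia is also one of the items of which two make PPC grade 2. Postoperative variables states: "The need for supplemental oxygen will be evaluated at each visit by measuring SpO_2_ and/or PaO_2_ after 10 min of breathing room air". Visits are twice a day to postoperative day 7. None of these passages asks for a comparison with the patient's state before surgery.

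**The concern.** The sentence that justifies the exclusion describes patients by their oxygenation. The criterion that carries it out describes them by their treatment. A patient with chronic lung disease and a room-air SpO2 below 90%, but without home oxygen or CPAP, fits the description of those to be excluded and still passes the chronic-lung-disease item.

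The endpoints make this more than a wording matter. The severity of respiratory failure and of PPCs are the key secondary objectives (Background), and both are meant to show what happened after surgery. A patient below the room-air threshold beforehand who stays below it is counted as a postoperative respiratory failure whatever ventilation was given. By the protocol's own reasoning, this is also the patient in whom sighs do least. Without a preoperative value, neither the grading nor the analysis can separate old hypoxemia from new.

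**Working it through.** **1. Following one patient through the rules.** Take chronic lung disease, room-air SpO2 of 88%, no home oxygen, no CPAP, and no other excluding condition.

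- Rationale sentence: belongs to the group to be excluded.
- Criterion list: not excluded, because the matching item depends on treatment.
- Listed baseline data: at most a history of COPD or asthma on inhaled therapy and abnormal imaging; no oxygenation value. The first recorded gas exchange is on the ventilator.
- Respiratory-failure scale: if SpO2 is still 88% on room air at a visit, at least mild, in either arm.
- PPC scale: one item towards grade 2. A second is needed, so hypoxemia alone does not give that grade.

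**2. The plan's own sample size.** Inputs from Sample size and power: control mean 294, SD 60, a 10% difference (0.10 × 294 = 29.4), power 90%, 5% dropout. The Statistical analysis section sets a two-sided 0.05 level. A two-sample t-test needs 88.5, so 89 per arm; 178 / 0.95 = 187.4, so 188 in total. This is close to the stated 192. With 96 × 0.95 ≈ 91 evaluable per arm, power is 0.908.

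**3. Illustration for the primary endpoint.** The document gives no prevalence of untreated chronic hypoxemia. Assume a share p of 2% to 8% (about 4 to 15 of 192) and zero benefit in this share. The effect becomes 29.4 × (1 − p). Two versions of the spread are shown: SD kept at 60, or SD = √(60² + p(1 − p) × 64²). The second assumes that these patients average 230, which is 64 below the planned 294.

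| p | Effect | Power, SD 60 | Widened SD | Power, widened SD |
|---|---|---|---|---|
| 0 | 29.4 | 0.908 | 60.0 | 0.908 |
| 2% | 28.8 | 0.896 | 60.7 | 0.890 |
| 5% | 27.9 | 0.878 | 61.6 | 0.860 |
| 8% | 27.0 | 0.856 | 62.5 | 0.828 |

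**4. Illustration for respiratory failure.** Assume true rates of any respiratory failure of 30% (control) and 15% (experimental) in everyone else, and that the share p is always graded at least mild. Each observed rate is p + (1 − p) × the true rate.

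| p | Control | Experimental | Risk difference | Risk ratio |
|---|---|---|---|---|
| 0 | 30.0% | 15.0% | 15.0 points | 0.50 |
| 2% | 31.4% | 16.7% | 14.7 points | 0.53 |
| 5% | 33.5% | 19.25% | 14.25 points | 0.57 |
| 8% | 35.6% | 21.8% | 13.8 points | 0.61 |

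Both rates rise by carried-over cases. The difference shrinks a little, and the ratio moves towards 1.

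**The case against.** The strongest reply is that the general sentence gives the reasons and the list gives the rules, so home oxygen or CPAP is simply the working definition of hypoxemia from chronic lung disease. It is easy to check and defensible. That stands as a reading, but the text does not say so, and the proxy is narrower than the sentence it implements. It also leaves the endpoint problem untouched, because the room-air threshold still has no preoperative reference.

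Three further objections limit the point.

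- A reader might infer that already hypoxemic patients do enter the trial. The document shows only that they could. Elective surgery, the limit on pulmonary systolic pressure and the sleep-apnea item will remove some of them.
- A reader might infer that no preoperative oxygenation is recorded anywhere. This cannot be established. The article condenses the full protocol, and neither the schedule figure nor the case report form is available. Only the absence from the article's baseline list can be stated.
- The prevalence, the mean of 230 and the zero benefit are assumptions; minimal impact is not zero. The planning SD of 60 may already include such patients, in which case widening it counts them twice.

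Finally, changing eligibility during recruitment is debatable, and the Discussion says that the definitions were chosen to allow comparison with earlier studies. Both are reasons to prefer an analysis-side remedy. Neither is a reason to leave the reference value out.

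**Conclusion.** The point holds in limited form. The stated intent is wider than the criterion, and the respiratory-failure scale, with one PPC item, can score hypoxemia that was present before surgery. The expected consequence is overcounted postoperative events and a diluted treatment effect on the key secondary scales. Randomization spreads these patients over both arms by chance, so the document does not support reading this as a bias in favor of either arm.

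The size is unknown and probably small. Under the assumptions shown, the respiratory-failure risk ratio moves from 0.50 to between 0.53 and 0.61. Primary-endpoint power falls from 0.91 to about 0.90 or 0.89 at 2%, and to between 0.86 and 0.83 only at 8%. A claim that the primary comparison is compromised would go beyond the evidence. The point merits action because the remedy is cheap and makes the secondary scales measure postoperative change.

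**What to change.** 1. Reconcile the rationale sentence with the listed criterion: either say that home oxygen or CPAP is the working definition of hypoxemia from chronic lung disease, or define the group by oxygenation.
2. Record preoperative room-air SpO2 for every patient at the existing preoperative visit, or from the chart for those already randomized. If the full case report form already holds this value, name it as the reference.
3. Before analysis, prespecify one of two uses. Either hypoxemia counts in the respiratory-failure and PPC scales only when it is new or worse than the preoperative value; or the published scales stay as they are, the preoperative value enters the planned multivariable ordinal logistic regression as a covariate, and new-or-worse grading is a sensitivity analysis.

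The cost is one data field and some chart retrieval, with possible gaps for patients already enrolled. Changing the scales themselves would also lose some comparability with earlier studies; the covariate option avoids that.
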